### Plans to promote participant retention and complete follow-up {18b}

To promote participants’ participation in the trial, blood glucose meters will be given to participants who participate throughout the trial. We will provide certain transportation subsidies for participants who come to the hospital for follow-up visits.

### Data management {19}

The data will be managed in accordance with the requirements established by law. All data collected will be identifiable so that participants can be contacted. During the recruitment process, each participant is given a unique study identification number. Participants will complete an online questionnaire using the Questionnaire Star (https://www.wjx.cn/), and the data of the Questionnaire Star will be authenticated and recorded over a secure network connection. All other information about the participants will be stored in a secure, password-protected computer.

### Confidentiality {27}

Only researchers and project leaders have access to the data and may not disclose subjects’ personal information to third parties without authorization. Participants will be assigned a unique trial identification number and their details will be stored on a password-protected computer. Upon signing the informed consent, the subject will be informed that the information may be reviewed by the relevant national administrative authorities and the ethics committee, but any public reporting of the results of this study will not disclose the personal identities of participants.

### Plans for collection, laboratory evaluation, and storage of biological specimens for genetic or molecular analysis in this trial/future use {33}

This study is designed to collect HbA_1c_ specimens. If there are any remaining blood samples, the testing company shall dispose of them in accordance with Chinese laws and regulations.

## Statistical methods

### Statistical methods for primary and secondary outcomes {20a}

Data will be analyzed applying SPSS 23.0 (IBM, Chicago, IL, USA). Data will be expressed as mean ± standard deviation or as *n* (%) in the case of categorical data, and differences between the four groups will be assessed for significance using the chi-squared test in the case, analysis of variance in the case, or non-parametric rank-sum test in the case of skewed continuous data. Differences between different time points within each group will be assessed for significance using generalized estimation equation. These models will include intervention variables, time as a categorical variable represented by dummy variables, the interaction between intervention and time, and baseline values. Differences associated with *P* < 0.05 will be considered significant.

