### Outcomes {12}

Data are collected at three times, including two follow-up visits at baseline, the 3rd month after intervention, and the 6th month after intervention, through participant visits to the hospital by the investigator.

The primary outcome is the level of HbA_1c_, which reflects blood glucose levels over the preceding 2–3 months and is a good indicator of blood glucose control [10, 11]. All results will be made by high-performance liquid chromatography at the same certified external laboratory to ensure consistency.

Secondary outcomes include frequency of blood glucose monitoring, body mass index, blood pressure, knowledge about diabetes, health beliefs related to diabetes, and diabetes self-management behavior. The App and the App + Reminder groups will also be asked about their satisfaction with the smartphone application.

The following questionnaires will be used for the study:

Change in knowledge from baseline as measured by the Chinese version of the Diabetes Knowledge Questionnaire (DKN) [12]. Each item is scored from 0 to 1, and the total scores range from 0 to 23 (Higher score indicating greater knowledge of diabetes)Change in health belief from baseline as measured by the Health Belief Questionnaire (HBQ) [13]. Scores ranging between 20 to 100 (higher score indicating better outcomes)Change in self-management behavior from baseline as measured by the Type 2 Diabetes Self-management Behavior Scale (2-DSCS) [14]. Total scores range from 26 to 130 (higher score indicating better outcomes)Custom-made questionnaire to assess user satisfaction with Dnurse application and its paired glucose meter. Participants who use the APP 6 months after the intervention will complete the assessment. The 5-level Likert scoring method is adopted, and the total scores range from 11 to 55 points (Table 2)

**Table 2 Tab2:** Custom-made questionnaire to assess user satisfaction with Dnurse application

Item	Very satisfied	Satisfied	Neither satisfied nor dissatisfied	Slightly dissatisfied	Very dissatisfied
1. Your satisfaction with the application interface					
2. Your satisfaction with the application’s ease of use					
3. Your satisfaction with how the application records blood glucose					
4. Your satisfaction with the health information provided by the application					
5. Your satisfaction with using the application to manage diabetes					
6. Your satisfaction with the application’s safety					

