### Sample size {14}

Using GPower 3.1 (University of Kiel, Kiel, Germany), this experiment is a factorial design, and the parameters required for this experiment are not found in previous studies. Based on the expected results of the experiment, a small effect size of 0.2 [15], two-sided A = 0.05, test power (1-β) of 0.9, and the F-test are taken to calculate the sample size of 220 cases. To compensate for an estimated 20% loss to follow-up, the final total sample size is 264 cases.

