## Data collection and management

### Plans for assessment and collection of outcomes {18a}

All participants will complete baseline assessments and complete follow-up at the 3rd and 6th month after the intervention.

At baseline, demographic data will be collected on age, sex, ethnicity, educational level, marital status, employment status, current residence, and method of paying for medical expenses. Data will be collected on the following clinical variables: chronic complications related to diabetes, such as hypertension, cardiovascular disease, cerebrovascular disease, peripheral vascular disease, kidney disease, peripheral neuropathy, eye disease and diabetic foot. Any chronic complications of diabetes that arise during the study will be recorded at the 6th month. Similarly, data on acute complications related to diabetes will be collected at baseline, such as hypoglycemia and lactic acidosis or ketoacidosis; and current diabetes treatments, including non-drug therapy, oral hypoglycemic drugs, and insulin therapy. Any acute complications of diabetes that arise during the study will be recorded at the 6th month.

At baseline and again at the 6th month, all participants will be asked to fill out three questionnaires. In addition, the App and the App + Reminder groups will fill out a fourth questionnaire at 6th month, which assesses their satisfaction with the smartphone application and glucose meter (Table 2). At baseline and again at the 3rd and 6th month, data will be collected on height, weight, blood pressure and HbA_1c_. At the 3rd and 6th month, all participants will be asked about their frequency of blood glucose monitoring.

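### Read literally, section {20a} tests between-group HbA1c differences without baseline HbA1c, and gives the only baseline-adjusted model to change within arms

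*Protocol article*

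**What the plan says.** Outcomes {12} states: "The primary outcome is the level of HbA_1c". It is defined as a level, not as a change. Section {18a} has it measured three times in everyone: "At baseline and again at the 3rd and 6th month, data will be collected on height, weight, blood pressure and HbA_1c".

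Section {20a} then divides the analysis into two tasks.

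- **Between groups:** "differences between the four groups will be assessed for significance using the chi-squared test in the case, analysis of variance in the case", or a rank-sum test where continuous data are skewed. No covariate is named.
- **Over time:** "Differences between different time points within each group will be assessed for significance using generalized estimation equation". The terms listed for this model are the intervention variables, categorical time, their interaction, and baseline values.

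No sentence says which analysis decides the primary question. The sample size section {14} uses "a small effect size of 0.2" with "two-sided A = 0.05, test power (1-β) of 0.9" and an F-test, and arrives at 220.

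**The concern.** The trial is designed for superiority, so its answer on HbA1c comes from comparing randomised groups. The only tests that {20a} assigns to that comparison have no baseline term. An analyst who follows the text would report an unadjusted ANOVA or rank-sum p-value for the group difference and use the adjusted model only to describe change within arms.

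Two things are lost. The month-6 variation that baseline HbA1c would explain stays in the error term, which widens the interval for the App effect. A chance difference in baseline HbA1c between arms also feeds partly into the month-6 difference. The data needed to avoid both are already collected. Section {17a} leaves the data analysts unblinded, so an unadjusted test and an adjusted model side by side, with neither named as deciding, also leave open which result will be reported.

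**Working it through.** **Inputs from {14}.** f = 0.2 (read as Cohen's f, because an F-test in GPower is named), two-sided alpha 0.05, target power 0.90, 220 evaluable participants, four equal groups.

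**Input not in the documents.** The correlation rho between baseline and month-6 HbA1c. It is assumed here, with range 0.3 to 0.7.

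**The plan's own figure.** Power of a fixed-effects F-test uses the noncentral F with lambda = N × f² and df2 = N − 4. For 90% power at f = 0.2 this needs 265 participants (1 df) or 359 (3 df), so 220 is not reproduced. At N = 220, lambda = 220 × 0.04 = 8.8 and power is 84.0% (1 df) or 69.2% (3 df). That shortfall is a separate matter. It is noted because it sets the starting point below.

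**Effect of adjustment.** A baseline covariate multiplies residual variance by 1 − rho². So f becomes 0.2/√(1 − rho²), lambda becomes 8.8/(1 − rho²), and df2 becomes N − 5.

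| rho | 1 − rho² | lambda | 1-df power (gain) | 3-df power (gain) |
|---|---|---|---|---|
| none | 1 | 8.80 | 0.8397 | 0.6917 |
| 0.3 | 0.91 | 9.67 | 0.8720 (+3.2) | 0.7369 (+4.5) |
| 0.4 | 0.84 | 10.48 | 0.8966 (+5.7) | 0.7741 (+8.2) |
| 0.5 | 0.75 | 11.73 | 0.9265 (+8.7) | 0.8236 (+13.2) |
| 0.6 | 0.64 | 13.75 | 0.9583 (+11.9) | 0.8841 (+19.2) |
| 0.7 | 0.51 | 17.25 | 0.9852 (+14.5) | 0.9472 (+25.6) |

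**Sensitivity to the starting point, at rho = 0.5.**

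- If all 264 are analysed, power goes from 89.9% to 96.2% (1 df, +6.3) or from 77.9% to 89.3% (3 df, +11.4).
- If the protocol's 90% at 220 is taken at face value, it rises to 96.3% (1 df) or 96.7% (3 df), a gain of 6 to 7 points.

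**Baseline imbalance.** With equal SDs at the two times, a chance baseline difference D shifts the expected unadjusted month-6 difference by rho × D: 0.3D, 0.5D and 0.7D at rho 0.3, 0.5 and 0.7. Randomisation makes D zero on average, so the test's type I error is unaffected.

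**Questionnaires.** {12} defines the knowledge, health-belief and self-management scores as change from baseline, so baseline already enters them. Relative to the outcome variance, a change score has variance 2(1 − rho) and ANCOVA has 1 − rho². At rho = 0.5 these are 1.00 and 0.75. Adjustment still helps, but for a different reason than with the HbA1c level.

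**The case against.** The strongest reply is that the adjustment is already in the paragraph. Intervention and intervention-by-time terms cannot be estimated from one arm alone. The listed GEE must therefore span all arms, and it can give baseline-adjusted contrasts at month 6. Its within-group label conflicts with its own terms. This stands: a reader might infer that the plan as a whole discards baseline HbA1c, and the documents do not support that. What remains is that the text does not give the GEE the between-group task and gives that task to tests without a covariate.

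A second reply is that nothing names ANOVA as the primary test. The sentence is garbled, it follows on from descriptive summaries, and a fuller analysis plan may settle the matter. It is right that no test is named as primary. However, the article does more than stay silent: it assigns four-group differences to specific unadjusted tests, and a later plan would have to depart from that wording.

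Third, the power gain depends on assumptions. This also stands. The 9 and 13 points at rho = 0.5 could be taken for a range, but they come from two different tests at a single assumed rho. Section {14} ties 0.2 to no HbA1c SD. If 0.2 was already standardised on an adjusted residual SD, there is no further gain to add.

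Two other inferences go too far. An imbalance does not pass in full into the month-6 difference, and the test is not invalid. Nor do the documents show that the rank-sum route will be used: {10} sets an HbA1c floor of 7.0% and no ceiling, which makes right skew plausible, but no distribution is given.

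**Conclusion.** The point holds as a matter of precision and clarity, not of validity. Taken at its word, {20a} compares HbA1c between groups without baseline and reserves the adjusted model for change within arms, although that model could supply the comparison needed.

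The size rests on three assumptions: rho between 0.3 and 0.7, 0.2 read as Cohen's f on the unadjusted SD, and N = 220 at alpha 0.05. On these, the forgone power is about 3 to 15 points for a 1-df contrast and about 5 to 26 for the 3-df four-group test. At rho = 0.3 the gain is small, and from the protocol's claimed 90% it is 6 to 7 points at rho = 0.5.

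**What to change.** In {20a}, state that between-group differences in HbA1c, and in the other continuous outcomes that have a baseline, are tested by the baseline-adjusted month-6 intervention contrast and reported with a 95% CI. Take the contrast either from the GEE already specified or from an ANCOVA of the month-6 value on randomised intervention plus the baseline value. Name which one is used. Monitoring frequency and satisfaction have no scheduled baseline measurement and are not affected.

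Handle skewness by transformation or robust standard errors, not by switching to an unadjusted rank-sum test. Keep ANOVA, rank-sum and chi-squared tests for descriptive or categorical comparisons.

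The cost is one sentence and one degree of freedom. No new data and no more participants are needed.

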### Objectives {7}

The aims of the study are to:

Evaluate the effect of the smartphone application Dnurse on glycemic management and disease control in individuals with T2DMAssess whether the application influences compliance with blood glucose monitoringMeasure user satisfaction with the application

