### Study design {8}

This will be a 2-center, factorial design, equal proportional distribution, superiority trial conducted in outpatient endocrinology clinics at two tertiary hospitals in Chengdu, China, which will be conducted from 2021 to 2023. 

In reporting the protocol for this study, we followed the SPIRIT 2013 checklist. Individuals will be randomly allocated to the Control group, Reminder group, App group, and App + Reminder group. Flow diagram of the study is shown in Fig. 1.

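### The factorial trial is meant to show superiority of the App, but section {20a} specifies no test of the App main effect

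*Protocol article*

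**What the plan says.** Study design {8} describes a "2-center, factorial design, equal proportional distribution, superiority trial" and names the four arms: "Individuals will be randomly allocated to the Control group, Reminder group, App group, and App + Reminder group". These are the four cells of App (yes/no) by Reminder (yes/no). The first aim in Objectives {7} is to "Evaluate the effect of the smartphone application Dnurse on glycemic management and disease control". Outcomes {12} fixes the endpoint: "The primary outcome is the level of HbA_1c_, which reflects blood glucose levels over the preceding 2–3 months". The abstract places its analysis after 6 months of intervention. Sample size {14} also rests on the statement that "this experiment is a factorial design".

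Statistical methods {20a} then gives each test a purpose. Between groups, "differences between the four groups will be assessed for significance using the chi-squared test in the case, analysis of variance in the case", with a rank-sum test for skewed data. For the longitudinal model, "Differences between different time points within each group will be assessed for significance using generalized estimation equation". The next sentence lists the model's terms: "These models will include intervention variables, time as a categorical variable represented by dummy variables, the interaction between intervention and time, and baseline values". No sentence names a comparison of App with no App pooled over Reminder, a Reminder main effect, or an App by Reminder interaction.

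**The concern.** The question the trial poses is a comparison of two halves of the sample: App and App + Reminder on one side, Control and Reminder on the other. The two tests that {20a} assigns answer other questions. The first asks whether the four arms are all alike. The second asks whether HbA1c changed over time inside an arm.

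Change inside an arm is especially uninformative here. Eligibility {10} admits people with HbA1c of at least 7.0%, so some regression towards lower values is likely. Every arm receives a glucose meter ({11a}), test strips are free ({11c}), and drug treatment may be changed during the trial ({11d}). HbA1c can therefore fall in any arm, Control included. A significant fall with the App beside a non-significant fall without it would still not be a comparison between them.

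Followed as written, the plan can report that the arms differ, or that HbA1c improved in App users. Neither supports a superiority claim. Because {17a} says the analysts are not blinded, leaving the decisive contrast to be chosen later also leaves room for a choice made after the data are seen.

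**Working it through.** **Step 1. Match each stated test to the question.**

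| Stated analysis in {20a} | What a significant result means | Does it isolate the App? |
|---|---|---|
| Comparison of the four groups | At least one arm differs from another | No: Reminder alone could cause it |
| GEE for time points within each group | HbA1c changed over time in that arm | No: there is no comparator |
| GEE terms as listed (intervention, intervention × time, baseline) | Could give a between-group App contrast | Possible, but no such use is stated |

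With either coding of the intervention, the App effect at month 6 is the contrast ½(App + App + Reminder arm means) − ½(Control + Reminder arm means). The model could supply it. {20a} does not ask for it.

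**Step 2. Inputs for the size of the problem.** Sample size {14} gives an effect size of 0.2, two-sided alpha 0.05, power 0.9, an F-test, 220 participants, and 264 after an allowance for loss. It does not name the effect-size metric. I assume Cohen's f because an F-test is used. I also assume that only the App has an effect, that the four-group ANOVA is one-way, and that there is no baseline adjustment, since no correlation is given.

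**Step 3. Formula.** Noncentrality λ = N × f², with f² = 0.2² = 0.04. Error df = N − 4. Power is the probability that a noncentral F with (df₁, N − 4) degrees of freedom exceeds the central F's 95% point. df₁ = 1 for the App contrast and 3 for the four-group test. If the App is the only effect, λ is the same for both tests.

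**Step 4. The plan's own figure.** At 90% power this formula needs N = 265 with df₁ = 1 and N = 359 with df₁ = 3. The stated 220 matches neither. That is a separate matter on which this point does not depend, but it means that {14} does not reveal which test was planned.

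**Step 5. Power at the stated sizes.**

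| N | λ | 1-df critical F | 1-df power | 3-df critical F | 3-df power | Difference |
|---|---|---|---|---|---|---|
| 220 | 220 × 0.04 = 8.80 | 3.885 | 84.0% | 2.646 | 69.2% | 14.8 points |
| 264 | 264 × 0.04 = 10.56 | 3.877 | 89.9% | 2.639 | 77.9% | 12.0 points |

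I show 264 because {20c} plans an intention-to-treat analysis with missing values filled by the last observation, so the analysed number would be close to the number randomised.

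**Step 6. What rejection by the four-group test would prove.** In the balanced design, λ depends only on f, not on which factor produces it. If Reminder alone had an effect of f = 0.2 and the App had none, the four-group test would still reject with probability 69.2% at N = 220 and 77.9% at N = 264.

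**The case against.** The strongest reply is that the GEE is already a between-group model. Comparing time points separately inside each arm would need no intervention terms, yet {20a} lists intervention variables, their interaction with time, and baseline values. The plural could well mean App and Reminder indicators. This stands in part. A reader might infer that the App effect is never tested or cannot be tested under this plan, and the documents do not support that. What remains is that the model's stated purpose is within-group comparison, that the coding is open, and that no App contrast is named.

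A second reply is that analysis of variance need not be one-way. In a factorial trial it may be two-way with 1-df main effects, and {14} links its F-test to the factorial design. The sentence in {20a} is also garbled and names neither HbA1c nor a primary test. This too is fair: the 3-df reading is the natural meaning of comparing four groups, but it is an inference. The power figures are therefore conditional.

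A third reply is that factor coding and contrasts are usually left to a statistical analysis plan, and that an article condenses the full protocol. That would answer a complaint about silence. Here the article does say which test serves which purpose, and the assignment does not fit the design.

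A reader might also infer an inflated false-positive rate from unadjusted pairwise comparisons of the arms. The documents plan no pairwise tests, so no such error rate can be charged to the plan.

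**Conclusion.** The point holds in this form: for a factorial superiority trial of the App, {20a} specifies no test of the App main effect, and the two uses of tests that it does state cannot show App superiority. This part rests on the text alone and needs no assumption about effect size.

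The loss of power is conditional. If the ANOVA is one-way, 0.2 is Cohen's f, Reminder has no effect and baseline is not adjusted for, the four-group test has about 69% power at N = 220 and 78% at N = 264. The 1-df App contrast has 84% and 90%. The gap is 12 to 15 percentage points, and the four-group test falls well short of the planned 90%. Baseline adjustment would change all four figures by an amount that the documents do not allow one to calculate.

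**What to change.** Rewrite {20a} before any analysis:

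- State that the baseline-adjusted model is used for between-group inference. Code App (yes/no) and Reminder (yes/no) as two factors and include their interaction. Use effect coding, so that the App coefficient is the main effect averaged over Reminder.
- Name one primary test: the 1-df contrast of App and App + Reminder against Control and Reminder, on HbA1c at month 6, two-sided 0.05. If the GEE with time terms is kept, say that the contrast is taken at month 6.
- Make the Reminder main effect and the App by Reminder interaction secondary.
- Report the App effect with and without Reminder, each with a 95% confidence interval, so that readers can judge whether pooling over Reminder is reasonable.
- Treat changes over time within an arm as descriptive.

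The listed GEE terms already come close to this model. The change costs wording in the protocol and analysis plan, and needs no new data or participants. Since the analysts are unblinded, it should be dated and fixed before they work with outcome data by arm.

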### Plans to promote participant retention and complete follow-up {11c}

To promote participants’ participation in the trial, blood glucose test strips will be given to participants free of charge during the trial.

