### Relevant concomitant care permitted or prohibited during the trial {11d}

Participants are allowed to go to the doctor or stay in the hospital normally during the trial, and the drug type and dose will be adjusted. If participants become pregnant during the trial, they will withdraw from the study.

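### Section {20a} aims its longitudinal model at change within each arm and gives those P values the same standing as the between-arm tests, although within-arm HbA1c change cannot isolate the App effect

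*Protocol article*

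**What the plan says.** Section {20a} of the protocol article plans two kinds of test.

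- Between arms: "differences between the four groups will be assessed for significance using the chi-squared test in the case", with analysis of variance or a rank-sum test for continuous data.
- Within arms: "Differences between different time points within each group will be assessed for significance using generalized estimation equation". The models are to hold the intervention variables, time as dummy variables, "the interaction between intervention and time, and baseline values".

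One sentence then covers both kinds: "Differences associated with *P* < 0.05 will be considered significant". Nothing ranks one above the other.

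Three other sections bear on how a within-arm HbA1c change can be read.

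- Section {10} admits people with HbA1c of at least 7.0%, and section {12} makes the same variable the endpoint: "The primary outcome is the level of HbA_1c".
- Section {11d} says of treatment during the trial that "the drug type and dose will be adjusted". Section {11c} adds that "blood glucose test strips will be given to participants free of charge during the trial", and section {11a} supplies a glucose meter in every arm, with a different model in the two App arms.
- On timing, section {18a} says "At baseline and again at the 3rd and 6th month, data will be collected on height, weight, blood pressure and HbA_1c". No separate screening HbA1c is listed, and no sentence says whether the qualifying value is the baseline value.

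**The concern.** The first objective in section {7} is the effect of the App, and section {8} describes a superiority trial. Only a comparison between randomised arms answers that question. A test of change inside one arm asks whether HbA1c moved at all, and in this trial it may move in every arm, Control included, for reasons unrelated to the App.

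The model best suited to the randomised question is the GEE, because it uses all visits and adjusts for baseline. The text gives it a different task. A significant fall in the App arm, or a significant fall there beside a non-significant one in Control, would carry the same label as a between-arm result. Setting two within-arm P values side by side is not a test of the difference between the arms.

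**Working it through.** The plan gives no figure on this point, so there is none to reproduce. The check asks how often an arm with no intervention effect would show a significant within-arm change.

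**Inputs from the article.** Entry threshold 7.0% ({10}). 264 participants in four equal arms ({14}, {8}), so 264/4 = 66 per arm. 20% loss to follow-up ({14}), so 0.2 × 66 = 13.2, taken as 13. Missing values replaced by the last one ({20c}). Significance at P < 0.05.

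**Assumptions, not in the article.** HbA1c is normal before selection, with mean 7.5% and SD 1.5. The correlation ρ between any two visits is 0.9 to 0.6. The qualifying value is the baseline. There is no intervention effect and no drug change.

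**Step 1, mean at entry.** a = (7.0 − 7.5)/1.5 = −0.333. φ(a)/(1 − Φ(a)) = 0.377/0.631 = 0.598. Mean of those selected = 7.5 + 1.5 × 0.598 = 8.40.

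**Step 2, expected fall from regression to the mean.** (1 − ρ) × (8.40 − 7.5).

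**Step 3, SD of change.** The variance at entry after selection is 1.5² × (1 + a × 0.598 − 0.598²) = 0.995. The SD of change is √[(1 − ρ)² × 0.995 + (1 − ρ²) × 2.25].

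**Step 4, chance of P < 0.05 with 66 in the arm.** Approximately Φ(z − 1.96), where z = fall × √66 / SD.

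| ρ | Fall (points) | SD of change | z | Φ(z − 1.96) | Simulated paired test |
|---|---|---|---|---|---|
| 0.9 | 0.09 | 0.66 | 1.10 | 20% | 19% |
| 0.8 | 0.18 | 0.92 | 1.58 | 35% | 34% |
| 0.7 | 0.27 | 1.11 | 1.97 | 50% | 49% |
| 0.6 | 0.36 | 1.26 | 2.31 | 64% | 62% |

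The simulated column uses 20,000 arms per row. Separate runs put the top row at 19% and the bottom row at 62% to 64%; I quote 19% to 63%. With 13 of 66 given their baseline value at month 6, the range is about 14% to 52% (16% to 53% in the 20,000-arm run). Moving the assumed source mean between 7.0% and 8.0%, with nothing carried forward, widens it to 12% to 87%.

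**Step 5, two such arms compared by their P values.** One is significant and the other not with probability 2p(1 − p). This is 31% at p = 0.19, 50% at p = 0.50 and 47% at p = 0.63.

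**Step 6, other readings of the same plan.**

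- If the baseline HbA1c is measured afresh after eligibility is settled, the within-arm test rejects in about 5% of arms. The regression artefact is gone.
- If baseline is only a covariate, so that the modelled visits are months 3 and 6, the month-3 versus month-6 test rejects in 4% to 6%.
- A between-arm comparison of change rejects in about 5%, even when the qualifying value is the baseline.

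**Step 7, common care alone.** Take a fresh baseline, 55 per arm (220/4) and an assumed fall of 0.3 points shared by all arms. An arm with no intervention effect is then significant in 31% (ρ = 0.5) to 90% (ρ = 0.9) of trials.

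**The case against.** The strongest reply is that the randomised comparison is already planned. The four-group tests come first in {20a}, the GEE includes the intervention-by-time and baseline terms, and the Discussion says the App will be benchmarked against routine care and telephone reminders. Selection and the supply of strips apply to all arms, so they cancel in the contrast between arms. All of this stands. It limits the point to the use assigned to the GEE and the status given to its within-arm P values.

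Three further replies carry weight.

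- A reader might infer that regression to the mean alone will make an arm look improved. The article does not support that. Table 1 puts the eligibility screen under enrolment and lists HbA1c only at 0, 3 and 6 months. Recruitment is partly by telephone from existing records ({15}), and trial HbA1c goes to one external laboratory ({12}). A fresh baseline is plausible. Section {16a} leaves the matter open.
- A reader might infer that the investigators will report a within-arm fall as an App effect. No section says so.
- The tested contrast is ambiguous. With baseline as a covariate, it may be month 3 against month 6. That reading cannot cover the knowledge, belief and self-management scales, which are collected only at baseline and month 6, so some within-group tests must start from baseline.

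Rejecting a null of no change that is truly false is also not a type I error. The risk is that a real change is attributed to the wrong cause. Finally, a 95% CI that excludes zero tells a reader much the same as a small P value, so removing the P value is not enough without a statement on interpretation.

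**Conclusion.** The point holds in a limited form. Section {20a} assigns its only longitudinal, baseline-adjusted model to tests within arms, and those tests cannot separate the App from care common to all arms or, possibly, from selection on HbA1c. If the qualifying value is the baseline, about 19% to 63% of arms of 66 with no intervention effect would show a significant baseline-to-month-6 change (about 14% to 52% with 13 carried forward). These figures rest on an assumed mean, SD and correlation. If baseline is fresh, that part is nil and what remains is common-care change, whose size the article does not allow one to estimate.

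It would go too far to say that the efficacy comparison is biased or that the plan relies on within-arm tests. The between-arm comparison stays at about 5%, and it is planned. The point is worth correcting because the remedy is nearly free. It does not undermine the trial.

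**What to change.** In {20a}:

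1. State that the GEE estimates between-arm contrasts: the App and Reminder effects through the intervention-by-time terms, adjusted for baseline, with month 6 as the inferential contrast.
2. Replace the within-group significance test by a description: mean change from baseline in each arm, with a 95% CI and no P value. This also suits the questionnaire scores. They are not selection variables, but their within-arm change is no more a randomised comparison than that of HbA1c.
3. Add a sentence that change within an arm is not evidence of an App effect.
4. Say whether the qualifying HbA1c is also the baseline value, so that readers can judge how much regression to the mean the descriptive changes may contain.

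The cost is a change of wording. The same model is fitted to the same data, and fewer P values are reported.
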